### Tracking of concomitant care during the trial {11d}

Participants will be permitted to receive concomitant care during study involvement. Concomitant care (e.g., medication, psychotherapy) will be measured during the post-intervention and follow-up surveys (i.e., “During the past 3 months, did you access any other mental health and/or parenting resources?”, “What resources did you access for mental health and/or parenting?”, and “How effective do you think these resources were?”).

### Sample size {14}

As this is a pilot and feasibility study, a sample size calculation is not appropriate. However, our target sample size of 30 participants per group is consistent with prior recommendations and will provide data to sufficiently establish BEAM feasibility [62, 63]. Accounting for a conservative 30% attrition rate [24], we will recruit an additional 10 participants per group (*N* = 80). With an estimated BEAM sample size of 40 mothers, we aim to achieve questionnaire completion and retention rates of 80% to within a 95% confidence interval of ± 12.4% as well as a treatment adherence rate of 50% to within a 95% confidence interval of ± 15.5%.

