***Aim 1***		
Recruitment rate	Number of mothers per week recruited	Mean 2 participants/week
Retention rate	% of mothers with data at follow-up	> 80% of mothers with follow-up data
Perceived usefulness	Usefulness subscale of mHealth App Usability Questionnaire	Mean score of < 3
Processing time	Time from initial contact until study enrollment	Mean time is < 1 week
Post-intervention questionnaire completion time	Time to complete post-intervention questionnaires	Mean of < 60 min to complete
Follow-Up questionnaire completion time	Time to complete follow-up questionnaires	Mean of < 60 min to complete
Questionnaire completion	% of missing data among program completers	> 80% of data is present among mothers who completed follow-up
Treatment adherence	Logging onto BEAM App and/or attending weekly group telehealth session	Participation in > 50% of program weeks via logging onto BEAM App or attending weekly group telehealth session
Safety	Adverse events from the BEAM program or assessments	No adverse events reported

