## Methods: assignment of interventions

### Allocation {16a–c}

Mothers will be randomized to the BEAM or MoodMission program with a 1:1 allocation. Randomization will occur in blocks of 10 using a computer-generated randomization schedule (http://www.randomlists.com/team-generator) stratified by participant availability for weekly group telehealth sessions. To conceal allocation sequence, randomization will occur once 10 mothers have been deemed eligible.

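### Forty per group leaves 28, not the target of 30, at the stated 30% attrition, and the ±12.4% precision does not carry over to questionnaire completion

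*Protocol article*

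**What the plan says.** The Sample size section of the protocol article declines a formal calculation, on the ground that this is a pilot and feasibility study. It sets a target by reference to earlier guidance: "our target sample size of 30 participants per group is consistent with prior recommendations". It then allows for loss: "Accounting for a conservative 30% attrition rate [24], we will recruit an additional 10 participants per group", for a total of 80. With the 1:1 ratio in the Allocation section, this is 40 per group.

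The section next gives expected precision. It opens with "With an estimated BEAM sample size of 40 mothers" and continues: "we aim to achieve questionnaire completion and retention rates of 80% to within a 95% confidence interval of ± 12.4" percent. For treatment adherence it gives a rate of 50% with a half-width of ±15.5%.

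Table 3 (Feasibility indicators) defines retention as the percentage of mothers with data at follow-up. For questionnaire completion, the success criterion is "> 80% of data is present among mothers who completed follow-up", while the indicator column of the same row refers to missing data among program completers. The text on Aim 1 under Outcomes defines completion as taking part in more than 50% of program weeks.

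**The concern.** Two stated figures do not follow from the plan's own inputs.

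First, the text presents the ten additional mothers per group as the allowance for 30% attrition. If they do not cover it, the expected number of completers falls below the target that the section adopts.

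Secondly, one half-width computed on all 40 BEAM mothers is used for an indicator that is measured only in a subset of them. Questionnaire completion is among the primary outcomes in the registration data set, and its success threshold is 80%. The stated interval therefore makes the estimate near that threshold look somewhat more precise than the design can deliver. Whoever plans the larger trial will read these figures as the expected yield and precision of the pilot.

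**Working it through.** **Inputs.** Target 30 per group, attrition 30%, 10 added per group, total 80, BEAM n = 40, planning rates 80% and 50% (all from Sample size); 1:1 ratio (Allocation); denominators for questionnaire completion (Table 3); 83.7% retention in a recent BEAM iteration (Strategies to improve adherence), for context only.

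**Attrition**

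- Expected completers per group: 40 × (1 − 0.30) = 28, or 56 in total against a target of 60.
- Attrition at which 40 leaves 30: 1 − 30/40 = 25%.
- Number needed to keep 30 after a 30% loss: 30/0.70 = 42.9, so 43 per group and 86 in total.
- Adding 30% to the target gives 30 × 1.30 = 39, close to 40. That method does not preserve 30, since 39 × 0.70 = 27.3. The document does not say how the ten was reached.
- If each mother independently has a 30% chance of loss, the exact binomial probability that at least 30 of 40 remain is about 0.31.

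**Precision: the plan's own figures**

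Half-width = 1.96 × √(p(1 − p)/n).

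- p = 0.80, n = 40: 1.96 × √(0.16/40) = 0.124, the stated ±12.4%.
- p = 0.50, n = 40: 1.96 × √(0.25/40) = 0.155, the stated ±15.5%.

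Both reproduce with all 40 BEAM mothers as the denominator. That is the right denominator for retention in the BEAM arm and for adherence.

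**Precision: questionnaire completion among follow-up completers in BEAM, p = 0.80**

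| Assumption | Mothers | Half-width |
|---|---|---|
| All 40 complete follow-up | 40 | ±12.4 points |
| 80% retention (same sentence of the plan) | 40 × 0.80 = 32 | 1.96 × √(0.16/32) = ±13.9 points |
| 30% attrition (preceding sentence) | 28 | 1.96 × √(0.16/28) = ±14.8 points |

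The first row requires no loss at all, which fits neither the 30% attrition nor the 80% retention in the section. If program completers are the denominator instead, the document gives no expected count for them. The 50% adherence rate is a planning value for precision, not a forecast, so I compute no interval for that case.

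**Limit of the method.** The criterion is the share of data present. A binomial interval with one observation per mother only approximates the precision of such a quantity. This applies to the ±12.4% as much as to the figures in the table.

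**The case against.** The strongest case on the other side is that little turns on this. Thirty is a rule-of-thumb target and no power statement depends on it. The plan calls 30% conservative, and at the 83.7% retention of the recent iteration 40 × 0.837 is about 33, above target. The clinical analyses are intent-to-treat with full information maximum likelihood, so they are not confined to completers. Table 3 sets its thresholds on means and percentages, not on confidence bounds, so a change of 1.5 to 2.4 points in a half-width alters no stated decision. All of this stands and limits the weight of the point. It does not make the sentence right: the stated target, attrition and recruitment figures still disagree.

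A reader might infer three stronger things that the document does not support.

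- *That retention should be judged on 80 mothers.* Table 3 does not name an arm in the retention row, but the precision sentence is explicitly tied to the BEAM arm. ±12.4% on 40 is correct for what it describes.
- *That ±14.8 is the one correct value for questionnaire completion.* It belongs to the 30% attrition assumption. The plan's 80% retention gives ±13.9, Table 3 names two different denominators, and the binomial form is approximate in any case.
- *That the trial should have enrolled 86.* The figure of 43 per group only measures the gap. Randomization is in blocks of 10, of which 86 is not a multiple, and the Trial status section reports that recruitment ended in March 2022.

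**Conclusion.** The point holds in two limited parts.

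1. At the stated 30% attrition the plan yields 28 completers per group, two short of its target. It reaches 30 only if attrition is no more than 25%.
2. The ±12.4% is too narrow for questionnaire completion as Table 3 defines it. With follow-up completers as the denominator, the half-width is about ±13.9 to ±14.8 points, that is 1.5 to 2.4 points wider. This rests on a rate of 80%, between 28 and 32 BEAM mothers completing follow-up, and one binomial observation per mother as an approximation.

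The ±12.4% for BEAM retention and the ±15.5% for adherence are correct. The two denominators given for questionnaire completion in Table 3 are an inconsistency in their own right: taking part in more than half of the program weeks and completing follow-up need not select the same mothers. The consequence is small, but these are stated figures for a primary outcome and for the size of the trial, and they should be put right.

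**What to change.** Change the wording only; recruitment is closed and no design element needs to move.

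- In Sample size, state that 40 per group leaves 28 per group at 30% attrition, or 30 per group at 25%.
- Keep ±12.4% for retention and ±15.5% for adherence, both for the BEAM arm with n = 40.
- In Table 3, choose one denominator for questionnaire completion and use it in both columns.
- Remove questionnaire completion from the ±12.4% statement and give its precision on the chosen denominator. If that is follow-up completers, state about ±13.9 points (32 mothers) to ±14.8 points (28 mothers), with a note that the interval is approximate because the criterion is a share of data present.

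The cost is a few sentences, and the stated figures become slightly less favourable.

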## Methods: assignment of interventions

### Allocation {16a–c}

Mothers will be randomized to the BEAM or MoodMission program with a 1:1 allocation. Randomization will occur in blocks of 10 using a computer-generated randomization schedule (http://www.randomlists.com/team-generator) stratified by participant availability for weekly group telehealth sessions. To conceal allocation sequence, randomization will occur once 10 mothers have been deemed eligible.

### Blinding {17a–b}

A research assistant unaffiliated with the BEAM clinical team will be responsible for conducting central randomization for participants who have agreed to participate and have received their identification number (i.e., following completion of pre-intervention questionnaires). The enrollment of mothers to the proposed study and their allocation to BEAM versus SOC will be completed by two separate research assistants. The research assistant designating treatment condition will have no interaction with participants (i.e., not on the BEAM clinical team). Trial participants, clinical coaches, parent coaches, and peer coaches will not be blinded to treatment condition given the behavioral nature of the treatment provided. Data analysts also will not be blinded to treatment condition.

## Methods: data collection, management, and analysis

### Data collection methods {18a–b}

An outline of all questionnaires to be used is presented in Table 2. Once a mother is randomized, all efforts will be made to follow the participant for the study duration. A recent iteration of BEAM for mothers of toddlers had an 83.7% retention rate [65], suggesting high retention rates are likely. Since this RCT will include an intent-to-treat analysis, participants will be encouraged to complete questionnaires regardless of program completion. Participants may withdraw from the study at any time, and the investigators may withdraw a participant to protect them and/or others in the program or if the study is terminated prior to the planned end date.

### Data management {19}

Participants will enter questionnaire responses in REDCap [31] which is managed by the Centre for Healthcare Innovation in Winnipeg, Manitoba, who are consultants on the proposed project. An administrative backup for roll-back purposes will occur daily, and data will be exported weekly and housed on an encrypted drive. Data quality checks will be conducted prior to analyses (e.g., range checks for data values). Data will be stored on a secure server in accordance with policies of the University of Manitoba’s REB and Personal Health Information Act (PHIA) policies.

### Statistical methods {20a}

All analyses will be conducted using IBM Statistical Package for the Social Sciences (SPSS). Descriptive statistics will be computed for the total sample and between the two groups (i.e., BEAM and MoodMission) for demographics and outcome measures at pre-intervention.

#### Aim 1

Descriptive statistics from back-end App data, telehealth group attendance, and questionnaires (i.e., BEAM App-Based, BEAM Forum, BEAM Perceived Social Support, BEAM Zoom Telehealth Group, mHealth App Usability, and MoodMission App-Based) will be used to examine program feasibility, engagement, and acceptability.

#### Aim 2

Data on maternal depression (PHQ-9) [35] and anxiety (GAD-7) [36] will be used to estimate effect size and variance for future sample size calculations. Preliminary analyses will also examine treatment effects on outcomes of interest (e.g., depression, anxiety). A longitudinal analysis of covariance, using linear mixed modelling, will be conducted to preliminarily test treatment effects on outcomes of interest. Treatment effects will be tested using two-way interactions between time and group assignment. Baseline moderation by symptom severity will be assessed to determine whether the BEAM program helps reduce symptoms for mothers with higher levels of depression and anxiety at pre-intervention compared to MoodMission. An *α* of 0.05 will determine statistical significance. Aggregate variables will be computed, by converting each measure to a standardized *z*-score then taking the average. Results will be reported as means and 95% confidence intervals for all comparisons. Bonferroni corrections are considered very conservative [64], and it has been suggested that correction may not be necessary, particularly if the study purpose is exploratory [65].

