##### The Building Emotional Awareness and Mental Health Program (Intervention Group)

The BEAM program was designed to promote intergenerational well-being through the treatment of maternal mental illness and preventing child mental health concerns, by integrating parenting and self-compassion skills with UP modules [16, 18]. The interrelated skills are designed to increase supportive parenting behaviors and promote maternal-child bonding to disrupt each of the theorized mechanisms of environmental risk transmission (e.g., positive emotional modelling, improved relationships, support for children’s distress, reduced conflict [15, 37]).

The BEAM program is a 10-week guided mental health and parenting program where participants move through modules with a cohort of other mothers experiencing depression and/or anxiety. Each week includes 10–30 min of psychoeducational video content, weekly mood tracking, a 1-hour weekly group telehealth session with content review and facilitated discussions in breakout rooms, access to an online forum to cultivate peer support, and assignments to practice key skills. The BEAM program content has been developed in collaboration with our PAB and the Family Dynamics team.

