###### Weekly group telehealth sessions

Weekly group telehealth sessions will provide mothers with the opportunity to discuss program material with coaches and peers, ask questions, and gain a sense of community. There will be three telehealth groups with different schedules to accommodate as many mothers as possible.

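### The Aim 2 model as described accounts for neither shared telehealth groups in the BEAM arm nor the availability stratum, so its 0.05 test is too liberal if outcomes correlate within groups

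*Protocol article*

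**What the plan says.** Design. Allocation {16a–c} says "Mothers will be randomized to the BEAM or MoodMission program with a 1:1 allocation", in blocks of 10, "stratified by participant availability for weekly group telehealth sessions". In the BEAM arm "participants move through modules with a cohort of other mothers experiencing depression and/or anxiety", with a one-hour group session each week. The section on these sessions adds: "There will be three telehealth groups with different schedules to accommodate as many mothers as possible". MoodMission users work alone and at their own pace.

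Analysis. Statistical methods {20a}, Aim 2, names the model class: "A longitudinal analysis of covariance, using linear mixed modelling, will be conducted to preliminarily test treatment effects on outcomes of interest". It then names the test: "Treatment effects will be tested using two-way interactions between time and group assignment". An alpha of 0.05 "will determine statistical significance". The PHQ-9 and GAD-7 data "will be used to estimate effect size and variance for future sample size calculations". Section {20c} adds maximum likelihood for missing data and one sensitivity analysis, restricted to completers.

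Use of the result. Table 3 makes a significant difference between arms in depression and anxiety the success criterion for treatment response.

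Neither the availability stratum nor the telehealth group appears in {20a} to {20c} as a covariate, a random effect or the subject of a sensitivity analysis.

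**The concern.** Mothers in one BEAM group share coaches, sessions and each other's support for ten weeks, so correlated outcomes are plausible. MoodMission has no such structure. This is a partially nested design, with clustering in one arm only. A mixed model whose random effects cover only repeated measures within a mother treats all BEAM mothers as independent. The confidence interval for the arm difference is then too narrow and the p-value too small. That p-value decides one of the Table 3 success criteria.

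The stratum is a separate and smaller matter. Leaving out a factor that randomisation has balanced costs precision.

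Aim 2 also exists to inform the size of the next trial. If group delivery inflates the variance of the BEAM mean and nothing in the report says so, planners could miss it.

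**Working it through.** **Inputs from the protocol article.** Sample size {14}: 40 mothers per arm recruited, 30 per arm as the evaluable target. Three telehealth groups. Alpha 0.05, taken as two-sided because sidedness is not stated.

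**Assumptions.** The article gives no ICC and no stratum effect, so both are shown as ranges. Here the ICC is the correlation between the analysed outcomes of two BEAM mothers in the same group. Groups are taken as equal in size.

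**The plan's own precision figures.** The half-width 1.96 × √(p(1−p)/40) gives 12.4% at p = 0.80 and 15.5% at p = 0.50, as stated in {14}. These are simple binomial figures that assume independent mothers. The article gives no standard error or power for Aim 2 to reproduce.

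**Clustering in the BEAM arm.** Mothers per group: m = 40/3 = 13.3. BEAM design effect: DE = 1 + (m−1) × ICC. With equal arms and only BEAM clustered, true SE / naive SE = √((DE+1)/2). Actual alpha = 2 × (1 − Φ(1.96 / ratio)).

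| ICC | DE | true/naive SE | actual alpha |
|---|---|---|---|
| 0 | 1.00 | 1.00 | 5.0% |
| 0.02 | 1.25 | 1.06 | 6.4% |
| 0.05 | 1.62 | 1.14 | 8.7% |
| 0.10 | 2.23 | 1.27 | 12.3% |

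Example at ICC 0.05: DE = 1 + 12.33 × 0.05 = 1.617; ratio = √(2.617/2) = 1.144; 1.96/1.144 = 1.714; alpha = 8.7%.

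With 30 per arm (m = 10) the ratios are 1.04, 1.11 and 1.20 and alpha is 6.0%, 7.7% and 10.4% at the same three ICCs.

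A simulation with groups of 14, 14 and 12, one post-treatment outcome and 8,000 trials per setting gave 6.8%, 8.8% and 12.4%.

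**Does adjusting for the stratum repair this?** No. In the same simulation at ICC 0.05, with each group drawn from one stratum, alpha was 8.8% without and 9.0% with a stratum main effect when the stratum explained nothing. It was 9.0% without and 9.7% with when the stratum explained 5% of the variance.

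**Omitting the stratum alone.** If the stratum explains a share R² of the variance and the arms are balanced within it, true/naive SE = √(1−R²). For R² of 0.02, 0.05 and 0.10 this is 0.990, 0.975 and 0.949, so the naive SE is about 1% to 5% too large and alpha is 4.8%, 4.4% and 3.9%.

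**The variance passed on.** The expected naive BEAM-arm variance, relative to the true total, is 1 − ICC × (m−1)/(n−1). At n = 40 this is 0.994, 0.984 and 0.968 for ICCs of 0.02, 0.05 and 0.10. Averaged with the unclustered arm, the pooled variance is low by 0.3%, 0.8% and 1.6%.

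**What a future calculation would lack.** As an illustration, a standardised difference of 0.5 at 80% power needs 63 per arm without clustering. Multiplying by (1+DE)/2 with m = 13.3 gives 71, 83 and 102 per arm at the three ICCs.

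**The case against.** The strongest objection is that the article is silent, not wrong. It names a model class and a test term but gives no closed list of covariates or random effects. A linear mixed model can hold both missing features, and a condensed article may leave such detail to a fuller plan. This stands in part. A reader might infer that the model excludes the stratum and the groups, and the text does not say that. The stratum half in particular is close to ordinary detail. Clustering in one arm only is different: it is a structural feature of the design, and the article does specify the test, the alpha level and the only sensitivity analysis without it.

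Second, the size of the problem rests on assumed ICCs, and at zero nothing changes. That is correct, and the figures are conditional on it.

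Third, this is a feasibility trial without a power calculation, and the Aim 2 tests are called preliminary. That limits the stakes but does not remove them, because Table 3 uses significance as a success criterion.

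Fourth, a reader might infer that the outcome variance handed to the next trial is materially wrong, or that the next trial will certainly be too small. Neither is supported. The variance is within about 2%, and the article does not say how that trial will be sized; its planners could bring in an external ICC.

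Finally, the article gives neither the number of availability strata nor how they map to the three telehealth groups. A one-to-one match is an assumption. The forum is not described as split by telehealth group, so it is not evidence for three clusters.

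**Conclusion.** The point holds in a conditional form. As described, the Aim 2 analysis accounts for neither the shared BEAM groups nor the randomisation stratum. For any positive within-group ICC the arm comparison is anti-conservative: over assumed ICCs of 0.02 to 0.10 with 40 per arm, the true SE is 6% to 27% above the naive one and a nominal 5% test runs at about 6.4% to 12.3%. The two omissions act in opposite directions and should not be merged, since the stratum's effect is small and conservative. The estimated outcome variance is close to right. What would be absent from a sample size based on it alone is the design effect. The change is worth making because it uses data already held, but it does not threaten the feasibility aims.

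**What to change.** 1. Include the availability stratum as a fixed effect in the Aim 2 models, and say that this is for precision and because randomisation used it, not as a remedy for clustering.

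2. Add a sensitivity analysis that recomputes the confidence interval and p-value of the arm comparison with a BEAM-only group effect, holding the ICC fixed at 0.02, 0.05 and 0.10. Fix it because three groups cannot usefully estimate an ICC.

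3. Report the effect size and variance for the next trial with the statement that the variance of the BEAM-arm mean must be multiplied by 1 + (m−1) × ICC over a stated ICC range, where m is the group size planned for that trial.

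Treatment differences within each stratum are not worth adding. With three equal strata they would rest on about 13 mothers per arm (40/3) and, if each stratum feeds one telehealth group, would confound treatment with that group.

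Cost: a few lines of text and code, a few degrees of freedom for the stratum, and wider intervals in the sensitivity analysis. No new data are needed.

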##### Pre-intervention questionnaires

All mothers deemed eligible to participate will be invited to complete a series of questionnaires via RedCap to assess baseline data of interest before allocation. See Table 2 for specific questionnaires.

**Table 2 Tab2:** Schedule for assessment administration

Study period					
**TIMEPOINT**	**Enrolment**	**Allocation**	**Intervention**	**Post-intervention**	**Follow-up**
	***Weeks 1–8***	**Week 9**	***Weeks 9–19***^v^	***Weeks 19–21***	***Weeks 32–34***
**Adverse Childhood Experiences**^**a**^	X				
**Ages and Stages Questionnaire: Social-Emotional, Second Edition** *(6, 12, 18, 24, 30, 36 months)*^b^	X			X	X
**Alcohol Use Disorder Identification Test**^**c**^	X			X	X
**Anxiety Persistence Scale**^a^				X	
**BEAM**^d^** App-Based Questionnaire**^a^				X	
**BEAM**^d^** Forum Questionnaire**^a^				X	
**BEAM**^d^** Perceived Social Support Questionnaire**^a^				X	
**BEAM**^d^** Zoom Telehealth Group Questionnaire**^a^				X	
**Cannabis, Tobacco, and Illicit Drug Use**^a^	X			X	X
**Cannabis Use Disorder Identification Test – Revised**^e^	X			X	X
**Couples Satisfaction Index – 4 Item**^f^	X			X	X
**Depression Persistence Scale**^a^	X				
**Depressive Symptom Index – Suicidality Subscale**^g^				X	X
**Emergency Health & Social Service Utilization**^a^	X			X	X
**Generalized Anxiety Disorder – 2 Item**^h^			X		
**Generalized Anxiety Disorder – 7 Item**^i^	X			X	X
**Infant Behavior Questionnaire – Very Short – Revised**^j^	X			X	X
**mHealth App Usability Questionnaire**^k^				X	
**Mini International Neuropsychiatric Interview**^l^	X				
**Mood Mission App-Based Questionnaire**				X	
**Parenting Scale** *(modified 10 item scale)*^m^				X	X
**Parenting Stress Index**^n^	X			X	X
**Parenting Stress Index** *(modified 4 item scale)*^a^			X		
**Patient Health Questionnaire – 2 Item**^o^			X		
**Patient Health Questionnaire – 9 Item**^p^	X			X	X
**Patient-Reported Outcomes Measurement Information System** *(Anger and Sleep Disturbance Subscales)*^q^	X			X	X
**Pediatric Quality of Life Inventory** *(1–12 or 13–24 months)*^r,s^	X			X	X
**Perceived Maternal Parenting Self-Efficacy Questionnaire**^t^	X			X	X
**Positive and Negative Affect Scale** *(modified 2-item scale)*^u^			X		
**Recent Stressful Experiences**^a^	X			X	X
**Sociodemographics**^a^	X				
**Substance Use Motives Measure** *(Coping Motive Subscales)*^v^	X			X	X

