### Criteria for discontinuing or modifying allocated interventions {11b}

Clinical coaches will receive an alert from REDCap [31] if suicidality items are endorsed during the pre-intervention, post-intervention, or follow-up surveys [i.e., endorsing “Thoughts that you would be better off dead or of hurting yourself in some way” on the PHQ-9 [35] or a 2 + on any items on the Depression Severity Index—Suicidality Subscale (DSI-SS) [43]] and/or during the psychodiagnostics mental health assessment. These alerts will prompt clinical coaches to take necessary steps to assess participant safety and provide appropriate intervention. The clinical team will consult on any instances of suicidality to determine whether it is in the participant’s best interest to continue in the study. Of those in the BEAM program, participants may have discontinued access to the online community forum and/or denied access to weekly group telehealth sessions if they repeatedly violate terms of use. Further, if a participant cannot maintain the confidentiality of others during weekly group telehealth sessions, they may be denied access. In the above case, participants will still have access to all psychoeducational materials on the BEAM app and will be invited to complete all questionnaires. Clinical coaches would also provide referrals to other clinicians and clinics, if appropriate.

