### Plans for collecting, assessing, reporting, and managing adverse events and harms {22}

No adverse experiences have occurred during the prior BEAM pilot study [24]. If participants report suicidality and/or self-harm risk, the clinical team will be notified. A risk management protocol will be in place where follow-up will occur among those identifying suicidality and/or self-harm. Clinical coaches will also follow-up with participants who identified suicidality on the online community forum and/or in weekly group telehealth sessions. The University of Manitoba’s standard procedures for reporting adverse events and protocol violations/deviations will be followed.

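### A between-arm excess of new or worsened suicidality is not assured to appear in the results, although the PHQ-9 self-harm item is collected in both arms at T1, T2 and T3

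*Protocol article*

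**What the plan says.** **Collection.** Trial design {8} has self-report data collected from both arms at T1, T2 and T3. Table 2 schedules the PHQ-9 at enrolment, post-intervention and follow-up. It schedules the "Depressive Symptom Index – Suicidality Subscale^g" (DSI-SS) at post-intervention and follow-up only.

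**Use for individual safety.** Section {11b} sends clinical coaches an alert "if suicidality items are endorsed during the pre-intervention, post-intervention, or follow-up surveys". The triggers are endorsement of the PHQ-9 item "Thoughts that you would be better off dead or of hurting yourself in some way" or a score of 2 or more on any DSI-SS item. Section {22} states: "If participants report suicidality and/or self-harm risk, the clinical team will be notified". Suicidality and self-harm are the only specific harms that section {22} names.

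**Use in analysis.** Outcomes {12} scores the PHQ-9 as a sum of nine items, each 0 to 3. Statistical methods {20a} states: "A longitudinal analysis of covariance, using linear mixed modelling, will be conducted to preliminarily test treatment effects on outcomes of interest". The treatment effect is the time-by-group interaction, and all comparisons are to be reported as means with 95% confidence intervals.

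**Safety outcome.** Safety is among the primary outcomes in the registration data set. In Table 3 its indicator is "Adverse events from the BEAM program or assessments", and success means that none is reported.

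**The concern.** The trial holds a randomised, same-schedule measure of the one harm that section {22} names, with a baseline. Two statements then decide how it reaches the results, and neither compares it by arm. {20a} fixes means as the format for comparisons, which absorbs the self-harm item into a total. Table 3 fixes Safety as events attributed to BEAM or to the assessments, and nothing ties that indicator to the alerts in {11b}.

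The attribution matters. Section {17a–b} leaves the coaches and the data analysts unblinded. Section {22} also describes detecting suicidality on the forum and in telehealth sessions, and only BEAM mothers have those. Event reports are therefore not gathered alike in the two arms, whereas the questionnaire items are.

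At stake is the safety part of the decision to proceed to the larger trial. As the plan stands, the report could show an improved mean PHQ-9 and no adverse events while more mothers in one arm, either arm, newly endorse thoughts of death or self-harm.

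**Working it through.** **Plan's own figures.** The plan gives no number for suicidality. Its stated precision for 40 BEAM mothers reproduces:
- 1.96 × √(0.8 × 0.2 / 40) = 0.124, the stated ±12.4%.
- 1.96 × √(0.5 × 0.5 / 40) = 0.155, the stated ±15.5%.

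**Inputs for the illustration.**
- 40 per arm (Sample size {14}) and 80% with data (the completion and retention rate in {14}): 0.8 × 40 = 32 per arm.
- PHQ-9 items scored 0 to 3, total 0 to 27 (Outcomes {12}).
- Assumed, because the document gives no figure: 5 BEAM and 1 MoodMission mothers newly endorse the item at T2; PHQ-9 SD of 4 to 6.

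**As counts.** 5/32 = 15.6% and 1/32 = 3.1%, a difference of 12.5 points. The Wilson limits are 6.9% to 31.8% and 0.6% to 15.7%. Newcombe's interval combines them:
- Lower: 0.125 − √[(0.156 − 0.069)² + (0.157 − 0.031)²] = −0.029.
- Upper: 0.125 + √[(0.318 − 0.156)² + (0.031 − 0.006)²] = 0.288.

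**As a shift in mean PHQ-9.** The excess is 5 − 1 = 4 mothers.
- Each up 1 category: 4 × 1 / 32 = 0.125 points.
- Each up 3 categories: 4 × 3 / 32 = 0.375 points.
- Standard error of the difference in means = SD × √(2/32) = 0.25 × SD, which is 1.0 for SD 4 and 1.5 for SD 6.

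The shift is well below one standard error throughout. More generally, a 10 to 20 percentage-point excess moves the mean by 0.1 to 0.6 points. With 28 to 40 per arm and SD 4 to 6, a simple two-group comparison detects that with a power of at most about 10%.

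**The mean can also point the other way.** If 4 of 40 mothers gain 2 points on the item while the other 36 improve by 1 more point overall, the arm's mean moves by (4 × 2 − 36 × 1) / 40 = −0.7. The arm with the excess looks better.

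**Does the DSI-SS fill the gap?** It measures suicidality alone, so its own mean is not diluted by other symptoms. But Table 2 gives it no T1 value:
- It cannot separate a new case from a mother who entered with ideation.
- On T2 and T3 alone, the time-by-group interaction is the arm difference at T3 minus that at T2. If the arms differ by the same amount D at both visits, the interaction is D − D = 0. It therefore does not test whether the arms differ at T2.

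**The case against.** **Safety is already a primary outcome.** Adverse events are reported under the university's procedures, and the article does not say that alerts fall outside them. Both arms complete the assessments, so the indicator is not confined to BEAM. This stands against any claim that an excess could not appear. It does not assure a comparison: the article does not say that alerts count as events, and worsening in the MoodMission arm that is not attributed to an assessment lies outside the indicator's wording.

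**Only an article is shown.** A safety table may sit in a fuller document, so its absence here is not a fault in itself. That is right. The point rests on what the article does fix: the format for all comparisons and the attribution-based Safety indicator.

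**Cases are acted on.** The clinical team considers whether each mother should continue, and the investigators review each phase. That protects individuals but does not compare the arms.

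**A table would have little power.** The 5 against 1 split is assumed and its interval includes zero. For 15% against 5%, Fisher's exact test has about 9% power at 30 per arm and 18% at 40. This stands, and it is why the table should be descriptive.

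**Stronger readings that the document does not support.**
- A reader might infer that suicidality is analysed only inside mean scores. The Safety outcome and the separate DSI-SS both count against that.
- A reader might infer that most answers will be zero because of the exclusions. Section {10} excludes a recent attempt or self-harm, not ideation, and {11b} expects some endorsement before the intervention. No baseline rate is given.
- A reader might infer from "Aggregate variables will be computed, by converting each measure to a standardized" score and averaged that the DSI-SS would be buried in a composite. The components are not listed, so this cannot be shown.

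**Conclusion.** The point holds in limited form. The self-harm item gives randomised data with a baseline, but {20a} absorbs it into a summed score reported as a mean, and Table 3 defines Safety without reference to the alerts. A between-arm excess of new or worsened suicidality is therefore not assured to appear in the results; the document does not support saying that it could not appear.

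The size depends on assumed counts and SDs. In the illustration, a 12.5-point excess moves mean PHQ-9 by 0.125 to 0.375 points against a standard error of 1.0 to 1.5. That the mean is a poor display for such an excess holds across the SDs and sample sizes tried. Nothing here suggests that an excess is likely in either arm. The change is worth making because it is cheap and bears on a primary outcome.

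**What to change.** In Statistical methods {20a}, add a descriptive safety table by randomised arm, over all randomised mothers with data, giving:
- (a) the number and percentage whose PHQ-9 self-harm item is newly endorsed or higher than at T1, at T2 and at T3;
- (b) the number and percentage meeting the plan's own DSI-SS alert level in {11b}, at T2 and T3.

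Give each between-arm difference with a 95% confidence interval and no test, and report the table beside the Table 3 Safety row. Part (a) identifies new or worsened cases; part (b) shows status only, for want of a T1 value. State which enrolment PHQ-9 supplies T1, since the eligibility screener also includes the scale.

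Cost: one paragraph and one table, with no new data, visits or staff, and no change to any clinical rule. Counts will be small and intervals wide: 6/40 against 2/40, for example, gives 10 points with a 95% CI of -4.0 to 24.5. Trial status estimates that primary outcome collection would be complete in December 2022, and this protocol version is dated February 2023. If the table is added after data collection, it must be labelled post hoc.
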